| Primary outcome:    | Proportion of participants receiving intravenous thrombolysis.                                                                                                                                                                                                                                                                                                                                                                                                                                                                                                            |
| Secondary outcomes: | 

• Stroke severity and complications at 24 hrs post thrombolysis

• Inpatient mortality

• Destination at discharge and 90 days

• Dependency at discharge and 90 days

• Assistance required at discharge and 90 days

• Time from emergency call and hospital admission to first brain imaging, thrombolysis, stroke unit admission, formal swallow assessment

• Patient experiences during the intervention pathway

• Professional views of the intervention pathway

 |
| Sample size:        | 1297 participants provide 90% power to detect a 10% difference in the proportion of patients receiving thrombolysis.                                                                                                                                                                                                                                                                                                                                                                                                                                                      |
| Study duration:     | 2.5 Years.                                                                                                                                                                                                                                                                                                                                                                                                                                                                                                                                                                |

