### **6.2 Objectives**

- To determine whether the PASTA pathway improves patient care and outcomes. Primary outcome: proportion of patients receiving intravenous thrombolysis. Secondary outcomes: stroke severity 24 hours after thrombolysis (National Institute of Health Stroke Scale (NIHSS)[21]), complications after thrombolysis, inpatient mortality, discharge destination, discharge dependency (modified Rankin Score (mRS)[22]), assistance at discharge, 90 day dependency (mRS), 90 day destination, assistance at 90 days.
- To describe the impact of the PASTA pathway on time intervals from emergency call and hospital admission to first brain imaging, thrombolysis treatment (if given), ASU admission and formal assessment of swallowing safety.
- To describe the number and subsequent diagnoses of suspected stroke patients who travelled to hospital with a study paramedic but following assessment at hospital were not given a diagnosis of stroke ('stroke mimics').
- To determine the cost-effectiveness of the PASTA pathway relative to standard NHS stroke care.

- To report patient experiences during the PASTA pathway, including confidence in the care process and information received about diagnosis and treatment.
- To report professional views and perspectives (paramedics and hospital staff) of the acceptability and feasibility of the PASTA pathway in the clinical setting.

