### **10.2 Standard stroke care (comparison group)**

Patients in the comparison group will receive standard stroke care as per current local ambulance and hospital clinical protocols, which are reinforced by national clinical guidelines and audit. The study will not provide comparison group paramedics with additional training or documentation to support information collection, clinical communication or processes after hospital arrival.

The local thrombolysis assessment and treatment processes in hospital will not be deliberately altered. It is routine practice that all patients receiving thrombolysis are observed for at least 24 hours and undergo repeat CT brain imaging at 24-48 hours to exclude intracranial haemorrhage. Recognised complications of thrombolysis include allergic reactions (angioedema), extra-cranial haemorrhage and intracranial haemorrhage causing symptomatic neurological deterioration (defined as with an increase in NIHSS  $\geq 4$  points within 36 hrs of thrombolysis associated with parenchymal haemorrhage on repeat brain imaging)[24].

Whether or not they receive thrombolysis, all patients with acute stroke should be admitted to an ASU within 4 hours of hospital arrival in order to receive specialist assessment and care tailored to their individual needs. The overall length of stay in hospital reflects pre-morbid conditions and dependency, stroke severity and subsequent medical complications (e.g. pneumonia, thromboembolism, stroke recurrence), progress during rehabilitation, personal social circumstances and the local availability of services to provide further rehabilitation and care in the community (including generic and stroke-specific early supported discharge teams and community rehabilitation teams).

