**Day 90 (+/- 7 days) data:**

At day 90, both data related to hospital discharge from this continuous inpatient episode and health at 90 days after stroke will be collected.

*Data related to discharge due to completion of all inpatient care:*

Died during this inpatient episode for stroke (yes/no)  
Cause of death  
Date of death (if relevant)  
Discharge date or record that the patient is still an inpatient at day 90 (yes/no)  
If still an inpatient at day 90, has there been stroke recurrence  
Discharge destination at completion of this inpatient episode (own home, different private address (eg relative) care home, other)  
If discharged to a care home, was the patient previously resident / not previously resident  
Rehabilitation arranged at discharge (none, early supported discharge team, community rehabilitation team, both)  
Assistance with activities of daily living required at discharge (yes/no; if yes: what support received: informal carers/paid carers/both)  
If paid carers then how many visits per week provided at discharge  
Dependency at discharge (mRS)

*Data related to day 90 health:*

Died after stroke event discharge but prior to 90 days (yes/no)  
Date of death (if relevant)  
Cause of death (if available)  
Readmission(s) to hospital since discharge; reason for admission(s), length of stay(s).  
Readmission was due to stroke recurrence (yes, no)  
Current (90 day) residence (hospital, home, different private address, care home, other).  
Current (90 day) dependency (simplified questionnaire mRS[25])  
Community rehabilitation since discharge (therapy received (yes/no); received at home/hospital/both; number of weeks received; less than, equal to or great than one appointment/week).  
Current (90 day) assistance with activities of daily living (yes / no; if yes: what support received: informal carers/paid carers (how many visits per week) /both)

For all participants, confirmation that stroke remains the diagnosis assigned for the event where consent was obtained. If not, the new diagnosis assigned.

Day 90 data consists of both routinely collected clinical data and study specific data. Routinely collected clinical data will be transcribed from routine medical records onto a study specific CRF. Study specific data will be collected by face to face interview, telephone interview or by postal questionnaire. Telephone interview with the participant or consultee will be the main method, undertaken by NHS research support staff.

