### **Recording and reporting of adverse events**

This study will only report adverse events which are considered to be serious.

In addition, apart from death, adverse events which are considered to be serious will only be reported up until seven days after study entry (ie for one week after the date of the paramedic assessment).

After seven days, there is no possible mechanism by which the study intervention can cause new adverse events. This approach mirrors other clinical trials of emergency stroke treatment where the longer term risk of unforeseen adverse events from the study intervention is very low. Any adverse events that do occur will be in the immediate peri-admission period as the intervention has been designed to facilitate the emergency administration of intravenous thrombolysis to appropriate stroke patients. Thrombolysis treatment is widely used in clinical practice and its adverse events are already well described. It can only be given once within 4.5 hours of stroke onset and has lost all pharmacological action within 24 hours. The study intervention does not change the clinical criteria for thrombolysis administration. Therefore it is not possible for any adverse events after the emergency phase to be attributed to the study intervention. To provide additional reassurance, the reporting period has been set at 7 days rather than just 24 hours.

Deaths will be recorded for the duration of a participants involvement in the study (until 90 days after stroke).

Serious Adverse Events will also **exclude**:

- The expected adverse events listed above (these will be routinely recorded and monitored as part of study data collection)
- Pre-planned hospitalisations and scheduled treatment for pre-existing conditions.

A study SAE form will be completed for all SAEs. To ensure complete capture of SAE's, the 90 day study CRF will include a question to ask staff to check for medical events that fulfil the criteria to be a SAE. For any events which fulfil the above criteria to be a SAE and are unreported, the study SAE form will be completed.

Serious adverse events, regardless of causality or expectedness, will be reported to the Chief Investigator. SAEs will also be reported to the trial sponsor (Newcastle Upon Tyne

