## 18. Statistical analysis

Analysis is by 'treatment allocated'; that is, primary and secondary efficacy and safety outcomes analyses will all use the study group allocation of the attending paramedic; only paramedics completing the study specific training will be considered as members of the intervention group. Thus, data will be analysed pragmatically according to paramedic group allocation, irrespective of the care process actually experienced by individual participants.

The primary end point measure is the proportion of participants who received intravenous thrombolysis. The primary analysis will compare the proportion of participants who received thrombolysis in the two arms of the study using logistic regression. Models will include various covariates and factors, including (but not limited to) participant age and gender and admission time and date (used to define a covariate to reflect background trends).

Secondary outcomes, including stroke severity 24 hours after thrombolysis (measured by an NIHSS score), inpatient mortality and dependency (modified Rankin Scale), will be analysed by appropriate ordinal and binary regression models, with appropriate adjustment for potential covariates and factors.

To address the second objective (that is, the impact of the intervention on various time intervals related to the emergency call), we will use appropriate statistical models. For time intervals between events which always happen (for instance, emergency call to hospital admission), we will employ linear models (after appropriate transformation), again adjusting for statistically significant covariates and factors; if the distributions of residuals are markedly non-normal, further transformation or bootstrapping will be considered. Residual diagnostics will also be used to identify outliers; identified outliers will be excluded and the analysis recalculated. For events which may or may not happen (for instance, emergency call to thrombolysis), we will analyse outcomes via binary regression models and survival analysis, comparing intervention and control arms using the framework of accelerated life testing; both approaches will again accommodate statistically significant covariates and factors.

Other clinical objectives will be addressed by appropriate descriptive statistical measures.

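### The only named mortality outcome stops at each patient's own discharge, although deaths are recorded to day 90; all-cause death by day 90 should be the mortality comparison.

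*Protocol*

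**What the plan says.** **Mortality.** Section 6.2 (Objectives) lists "complications after thrombolysis, inpatient mortality, discharge destination, discharge dependency (modified Rankin Score (mRS)[22]), assistance at discharge". The Protocol summary (section 4) also names inpatient mortality and no other mortality outcome. Section 18 (Statistical analysis) takes it to formal comparison: "inpatient mortality and dependency (modified Rankin Scale), will be analysed by appropriate ordinal and binary regression models".

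**Window.** Section 13 (Day 90 data) ties the discharge items to the end of all inpatient care and asks for "Discharge date or record that the patient is still an inpatient at day 90 (yes/no". Inpatient death is thus counted over a period that differs from patient to patient. Section 10.2 says what drives that period: "The overall length of stay in hospital reflects pre-morbid conditions and dependency, stroke severity and subsequent medical complications", and goes on to include social circumstances and the local availability of community services.

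**What else is collected.** Section 13 also records "Died after stroke event discharge but prior to 90 days (yes/no", with the date of death. Section 17 adds "Deaths will be recorded for the duration of a participants involvement in the study (until 90 days after stroke". Where the 90-day study data have not been obtained by six months, section 13 has staff re-confirm from hospital systems whether the participant was alive at 90 days.

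**Disability outcomes.** These are fixed at two times. Section 6.2 continues with "90 day dependency (mRS), 90 day destination, assistance at 90 days", and the summary has "Dependency at discharge and 90 days", with the same pairing for destination and assistance. Section 13 scores death as 6 on the modified Rankin Scale (mRS).

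**The concern.** The first objective asks whether the pathway improves patient outcomes, and the only outcome offered for survival is one whose exposure time is not fixed. Take two patients who both die on day 20. The one still in hospital counts as an inpatient death; the one already discharged counts as an inpatient survivor. Where a patient is on day 20 depends partly on family circumstances and local services, which are not health outcomes.

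The window may also respond to the intervention. Section 5 (Background) expects faster treatment to reduce dependency, and section 10.2 lists dependency among the determinants of stay. If the pathway shortens stay, it also shortens the period in which intervention-arm deaths are counted. That would tilt inpatient mortality in favour of the intervention even if 90-day mortality were equal.

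At stake is the reading of one secondary outcome that many readers will look at early: a lower inpatient mortality could not be cleanly read as better survival. Dependency, assistance and destination at discharge share the weakness in milder form, because they are read at different stages of recovery in different patients.

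**Working it through.** **1. What the protocol fixes.** It gives no expected inpatient or 90-day mortality by arm and no length of stay, so there is no figure of its own to reproduce here. The nearest is the national average inpatient mortality of 17% in section 17. The planned analysable numbers in the Sample size section are 856 control and 428 intervention, with mean cluster size 5 and intra-cluster correlation 0.02.

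**2. Scale at trial size.** Design effect = 1 + (5 − 1) × 0.02 = 1.08. With 17% in both arms, the standard error of the difference is √[0.17 × 0.83 × (1/856 + 1/428) × 1.08] = 0.0231, or 2.3 percentage points. The 95% interval half-width is 1.96 × 2.31 = 4.5 points.

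**3. Size of an artefact, first illustration.** These are assumptions, not protocol figures. Both arms have the same probability D of death by day 90. Time of death is exponential with parameter 1/a days, truncated at 90. Stay is exponential with mean 1/b days and unrelated to death. Then

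P(inpatient death) = D × [a/(a + b)] × [1 − exp(−90(a + b))] / [1 − exp(−90a)].

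Example with D = 0.20 and a = 1/15:
- mean stay 20 days: 0.20 × 0.5714 × 1.0025 = 11.5%
- mean stay 15 days: 0.20 × 0.5000 × 1.0025 = 10.0%
- apparent gap 1.4 points (unrounded); true 90-day gap 0.

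Range over D = 15% to 25% and 1/a = 15 or 25 days:

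| Mean stay, control v intervention | Apparent gap (points) |
|---|---|
| 20 v 18 days | 0.4 to 0.7 |
| 20 v 15 days | 1.1 to 1.8 |
| 20 v 12 days | 1.9 to 3.2 |

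**4. Second illustration, different shapes.** Assume 22% dead by day 90 in both arms, Weibull death times (shape 0.6, scale 18 days) conditional on death by day 90, and log-normal stay (SD of log 1.1). Simulated inpatient mortality is 10.8%, 12.3%, 13.7% and 15.3% at median stays of 7, 10, 14 and 20 days. Stays of 14 v 10 days give a gap of about 1.5 points, and 20 v 7 days about 4.5 points.

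**5. A modest shift.** The Sample size section postulates 10 more patients per 100 thrombolysed (0.43 to 0.53). If only that 10% had their median stay halved from 14 to 7 days, the gap would be 0.10 × (13.7 − 10.8) = 0.29 points, or 0.29/2.31 = 0.13 standard errors.

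**6. Chance of a misleading result.** The probability of a significant result in the direction of the artefact is Φ(gap/2.31 − 1.96). Gaps of 1, 2 and 3 points give about 6%, 14% and 25%, against 2.5% with no gap.

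**7. Is the alternative available?** Setting the three sources side by side: death after discharge with its date (section 13), deaths recorded to day 90 (section 17), and vital status re-confirmed where the 90-day data are missing (section 13). Together they give all-cause death by day 90 without a new data item. As the outcomes are named, these later deaths enter a between-arm comparison only as mRS 6 within 90-day dependency.

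**The case against.** **Fixed-time outcomes already exist.** A reader might infer from the discharge list that disability is compared only at discharge. The documents do not support that: dependency, destination and assistance at day 90 are named secondary outcomes in both the summary and section 6.2. This stands in full and limits the point to mortality, with a remark on how to read the discharge measures.

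**Deaths after discharge are not ignored.** They score 6 in the 90-day mRS, and section 18 introduces its secondary outcomes as examples rather than a closed list. This stands in part. A death merged with disability is not a mortality comparison, and the one mortality outcome the protocol names, in three places, is still cut at discharge.

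**Stay need not differ between arms.** Section 9 randomises stations or teams within each ambulance service, so local discharge practice is not systematically tied to arm. If the pathway shortens stay by reducing dependency, patients are not faring the same in every respect. This also stands in part: variation in local services mainly adds noise, and the documents neither show nor exclude a difference in stay. A pathway can, however, reduce dependency without changing survival, and inpatient mortality would then still move.

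**The illustrations may overstate.** Their inpatient mortality (5.0% to 15.3%) is below the 17% in section 17, which puts too many deaths after discharge. They also treat stay as unrelated to death, although section 12 says early deaths are usually identified on admission and treated palliatively. Both criticisms are fair.

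**Discharge measures have wider coverage.** Under section 12, participants entered by an independent clinician are not contacted at day 90, and survivors entered under the palliative declaration have no day-90 assessment. Discharge data from routine records can cover them. This is a sound reason to keep the discharge measures. It does not apply to 90-day death, which can be taken from records.

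**Conclusion.** The point holds for mortality. The protocol's only named mortality outcome has a patient-specific window that depends partly on non-health factors and could respond to the intervention, while the data for a fixed 90-day comparison are already collected.

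Its size cannot be derived from the documents. Under the assumptions above it runs from about 0.3 points, if a tenth of patients have much shorter stays, to about 4.5 points if whole-arm median stay were 20 v 7 days. The lower part of that range is small beside a standard error of 2.3 points; the top needs a difference in stay that nothing in the protocol suggests. A reader might infer that the trial will show a false mortality benefit. The documents do not support that; they support only that a difference in inpatient mortality could not be cleanly attributed to survival.

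Only secondary outcomes are affected. The primary outcome, receipt of thrombolysis, is not.

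**What to change.** In section 4, section 6.2 and section 18, name death from any cause by day 90 as the mortality comparison, with time to death to day 90 as its companion, using the dates already collected. Report inpatient death as supporting description beside length of stay by arm.

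Keep dependency, destination and assistance at discharge, state that they are to be interpreted alongside length of stay, and say that the day-90 versions are the main reading.

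The cost is an amendment to one named secondary outcome, made after the primary outcome has already been changed once, so the reason should be recorded and the change dated before any comparison by arm. No new data collection is needed. Inpatient death remains reported, so comparison with national audit figures is not lost.

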## **7. Study design**

The study design is a cluster randomised controlled trial (RCT) with internal pilot phase and parallel process evaluation. Participants will receive either the PASTA pathway (intervention group) or standard stroke care (comparison group).

## **8. Study setting**

The study will take place within ambulance services and a selected number of receiving hospital sites. Hospital sites within each region will be selected to represent a range of service designs and historical efficiencies in the provision of acute stroke care. All sites will already be receiving emergency stroke admissions and can provide 24 hour access to brain imaging and a stroke specialist opinion in order to make a thrombolysis decision. The research environment will reflect the local care pathway for patients with acute stroke symptoms and will include the scene of the incident, ambulance, ED, radiology department and ASU.

## **9. Randomisation**

PASTA is a cluster RCT in which the unit of randomisation is an ambulance station or, in the case of large ambulance stations, an identifiable paramedic team within a station. Clusters comprise the paramedics based within teams or at stations. Randomisation will be performed prior to the start of the trial in each region. Within each ambulance service, ambulance stations or paramedic teams (according to local service configuration) which feed into a study hospital will be randomised to delivering the PASTA pathway or to continue with standard stroke care. All paramedics will be given the option of not assisting with the study.

Stations or teams within each service will be stratified according to size (categorised as small, medium or large according to the personnel and resources available), and distance from the nearest study hospital admitting stroke patients (distance categorised as near or far, reflecting the local geography of each ambulance service). The use of these stratifying variables will ensure that PASTA care paramedics (intervention) and standard care paramedics (control) are approximately equally matched by operational characteristics. The actual randomisations will be performed, documented and reported by two statisticians at Swansea University Clinical Trials Unit.

Stations and teams randomised to continuing standard care will be informed that there is an ongoing study of pre-hospital assessment for stroke patients, but not be given any further information about the intervention. For paramedics who are part of a station or team randomised to deliver the PASTA pathway, study specific training and documentation will be provided. Paramedics who opt out of the study or who work within a station or team that was not selected to be involved in the study will continue to deliver standard care.

